### Secondary outcomes

#### Fatigue

Fatigue will be assessed using two scales. The first scale used is for emotional exhaustion - the UBOS G(eneral) [20]. The Utrecht Burnout Scale UBOS is the Dutch version of the Maslach Burnout Inventory. This study uses only the emotional exhaustion subscale.

The second variable is the Need for Recovery after work scale of the Dutch Experience and Evaluation of Work Questionnaire (Dutch: VBBA, Meijman and Van Veldhoven, 1994) [21]. The scale measures work-related fatigue as the extent to which employees experience problems in recovery efforts from work. The Need for Recovery after work scale score is calculated by adding the individual’s scores on the eleven (recoded) items. This scale score is transformed into a scale ranging from 0 to 100. Higher scores indicate a higher degree of need for recovery after work.

#### Stress

Stress will be measured using the distress subscale of the Four-Dimensional Symptoms Questionnaire (4DSQ) [22]. The 16-item questionnaire uses a 5-point response scale (0 = *no*, 4 = *very often*) and has a Cronbach’s alpha of 0.90.

The accumulation of the stress level of an individual is measured by the stress hormone cortisol in hair. Hair cortisol reflects the cumulative responses over time of cortisol in the body [23]. Using measurements of head hair makes it possible to determine accurately the level of experienced stress that has accumulated over a long period. Hair strands in the posterior vertex region are cut as close as possible to the scalp using iron scissors. Cortisol concentrations will be determined from a 3-cm hair segment. Based on an average hair growth rate of 1 cm per month [24], each hair segment reflects hair grown over approximately 3 months. In this study, cortisol concentrations in the last month are determined at baseline (T0) and after 12 weeks (T2).

#### Quality of life

The Dutch version of the SF36 questionnaire [25] is used to measure the quality of life. This study assesses three dimensions: (i) vitality; (ii) role limitations due to personal or emotional well-being; and (iii) social functioning. For each variable item, scores are coded, summed, and transformed to a scale from 0 (worst possible health state measured by the questionnaire) to 100 (best possible health state measured by the questionnaire).

### Other study parameters

#### Socio-demographic variables

At baseline, socio-demographic data such as age, gender and job title will be collected by the research assistants by means of an interview.

#### Statistical analysis

Data will be analysed using the statistical package IBM SPSS Statistics 22. The baseline data and the data from T1, T2 and T3 will be analysed and stored in a databank. The longitudinal analysis will be used to examine differences between the three arms with regard to improvement of the primary outcome (return to work) and the secondary outcomes of stress, fatigue and quality of life.

#### Sample size

The sample size is based on a medium effect size on the primary outcome of the intervention, return to work. Changes in the outcome measures are measured across the three groups and four measuring points by comparing them at the start of the study (T0) with the outcome measures after the end of the measurement period (T3). In order to determine the differences within and between the four measurement points, a multilevel regression analysis is conducted. For a power of 0.80 with an effect size of f = 0.3, the number of participants required is *N* = 79, with *N* = 90 being a desirable starting figure.

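### The analysis is described as T0-to-T3 improvement with T0 as a measuring point; adjusting follow-up for T0 is never asymptotically less precise and removes chance baseline imbalance

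*Protocol article*

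**What the plan says.** In the protocol article, Statistical analysis says that a longitudinal analysis will "examine differences between the three arms with regard to improvement of the primary outcome". The same sentence covers stress, fatigue and quality of life.

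Sample size gives more detail: "Changes in the outcome measures are measured across the three groups and four measuring points", and this is done "by comparing them at the start of the study (T0) with the outcome measures after the end of the measurement period (T3". The model follows: "In order to determine the differences within and between the four measurement points, a multilevel regression analysis is conducted". The count of four is reached only if T0 is one of the points.

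Primary outcome defines return to work as hours at the end of the study set against hours in the week before T0, with hours recorded at T0, T2 and T3. Informed consent and randomization places allocation after the baseline measurements. None of these sections names T0 as a covariate or says that arm means are held equal at T0.

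**The concern.** Because T0 precedes allocation, the three arms share one true mean there. A model that still estimates a separate T0 mean for each arm spends information on differences known to be chance. With complete data its T3 contrast is the difference in mean change. That contrast fixes the slope of follow-up on baseline at 1, whatever the true slope is.

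Two things are at stake. The first is precision, in a trial with about 30 per arm. The second is that an arm that happens to start higher or lower will appear to improve less or more for that reason alone. The T0 value that would deal with both is already collected for the primary and secondary outcomes.

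**Working it through.** **The plan's own figure.** Sample size gives N = 79 "For a power of 0.80 with an effect size of f = 0.3". Alpha and the within-person correlation are not stated, so 79 cannot be derived from the text alone. Assuming alpha 0.05, a one-way comparison of three groups at f = 0.3 needs 111. A repeated-measures between-groups test with four points and correlation 0.6 needs exactly 79. The figure is attainable but unverified, and nothing below depends on it.

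**Inputs.** From the document: 90 participants in three equal groups, so 30 per arm; T0 before randomization; entry restricted to at least 50% absence. Assumed, because not given: ρ, the correlation of T0 with T3, and k = SD(T0)/SD(T3). I take k = 1 as plausible for the questionnaire scales, and k = 0.5 for hours worked if the entry criterion compresses T0.

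**Variance per participant, in units of the T3 variance.**
- Change score: 1 + k² − 2ρk
- Adjusted for T0: 1 − ρ²
- Excess of change over adjusted: k² − 2ρk + ρ² = (k − ρ)², which is never negative and is zero only when ρ = k

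**Chance imbalance.** The T0 difference between two arms of 30 has SD √(2/30) = 0.258 in T0 SD units. Given that difference, the change contrast is shifted by an amount whose SD is |k − ρ| × 0.258 in T3 SD units. With k = 1 this is (1 − ρ) × 0.258.

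| k | ρ | Change | Adjusted | Variance reduction | Imbalance carried into change (T3 SD units) |
|---|---|---|---|---|---|
| 1 | 0.3 | 1.40 | 0.91 | 35% | 0.18 |
| 1 | 0.5 | 1.00 | 0.75 | 25% | 0.13 |
| 1 | 0.7 | 0.60 | 0.51 | 15% | 0.08 |
| 0.5 | 0 | 1.25 | 1.00 | 20% | 0.13 |
| 0.5 | 0.3 | 0.95 | 0.91 | 4% | 0.05 |
| 0.5 | 0.5 | 0.75 | 0.75 | 0% | 0 |
| 0.5 | 0.7 | 0.55 | 0.51 | 7% | 0.05 (direction reversed) |

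**Check within a longitudinal model.** Generalized least squares with k = 1 compared T0 means free by arm with one common T0 mean. The ratio of standard errors (common to free) was 0.81, 0.87 and 0.92 at ρ = 0.3, 0.5 and 0.7. These are the square roots of 0.65, 0.75 and 0.85, so they match the table. With T0 kept as a response, the common mean is therefore what recovers the precision.

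**The case against.** **The text does not specify a full model.** It names a multilevel regression without fixed effects or contrasts, and part of the wording sits under Sample size. A model with T0 as a response and one common T0 mean would fit the text. A reader might infer that the plan rules out baseline adjustment; it does not, and a fuller protocol or analysis plan may provide for it. What remains is that every statement in the article treats T0 as a reference for change or as a measuring point, and the most direct reading is a change contrast.

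**The gain for the primary outcome may be close to nil.** This stands. If the T0 SD for hours is about half the T3 SD, the table shows little to gain at correlations between 0.3 and 0.7. The larger gains belong to the questionnaire scales, and only under equal SDs.

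**Change is unbiased.** Over repeated randomization it is. The imbalance problem is conditional on the arms actually drawn. The 0.26 SD is also the raw T0 difference; only the part in the last column of the table reaches the estimate.

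**Power.** A reader might infer that the trial already falls short of its stated power, or might turn the variance reductions into power gains. The documents support neither. The planned N can be reproduced under some repeated-measures assumptions. The effect size f = 0.3 is given for return to work, whereas equal SDs suit the questionnaires, so no outcome has both inputs supported.

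**Conclusion.** The point holds as an improvement that should be made, not as a demonstrated error. As described, the analysis is of change from T0 with no stated baseline adjustment or common T0 mean. Adjusting for T0 cannot do worse in asymptotic variance, for any correlation or SD ratio; in a finite sample it costs the estimation of one slope.

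The size rests entirely on assumed correlations and SD ratios. It is a variance reduction of 15% to 35% for scales with equal SDs and correlations of 0.3 to 0.7, and between nil and about 20% for hours worked if the T0 SD is halved. Adjustment also removes a conditional shift with an SD of roughly 0.08 to 0.18 in the equal-SD case. The case is firmest for the questionnaire outcomes and may matter little for return to work.

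**What to change.** State in the Statistical analysis section that the multilevel model takes the follow-up values as responses, with the participant's T0 value as a covariate and terms for arm, visit and arm × visit. The primary contrast is read at T3. The responses would be:
- hours worked: T2 and T3, since Primary outcome schedules no measurement at T1;
- questionnaire scales: each follow-up visit at which they are measured;
- hair cortisol: T2 only, because it has no T3 value.

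Alternatively, keep T0 in the outcome vector and constrain the arm means to be equal there, by letting arm terms enter only at the follow-up visits. Either form should be fixed before outcomes are examined by arm, so that there is no later choice between change and adjusted results.

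The cost is a sentence or two of analysis wording. No new data or extra visits are needed, and the named software can fit the model.

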### Informed consent and randomization

Randomization (Fig. 2) will take place once the participant meets the inclusion criteria, has read the written information about the study and has given written informed consent after approval and after the baseline measurements. Preliminary numbers are assigned to the three groups of equal size in the study. Participants receive a random number from a research assistant who is not involved in the actual measurements. These numbers are printed on the measuring instruments. Participants are given a random number on the basis of entry and assigned to one of the three groups.

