### Outcomes

#### Primary outcome

The primary outcome variable is the percentage return to work: the number of contract hours that participants work at the end of the study compared to the number of contract hours worked in the week prior to the study (T0). The number of hours worked will be measured at T0 (start), T2 (after 12 weeks) and T3 (after 24 weeks).

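### The 0.80 power at f = 0.3 with N = 79 is tied to four measuring points the primary outcome does not have; on the single end-versus-T0 value, without a baseline gain, it is 0.64 (0.71 at N = 90)

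*Protocol article*

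**What the plan says.** All references are to the protocol article.

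- **Sample size**, on the basis of the calculation: "The sample size is based on a medium effect size on the primary outcome of the intervention, return to work".
- **Sample size**, on the structure: "Changes in the outcome measures are measured across the three groups and four measuring points". The contrast it then describes is T0 against T3, and a multilevel regression is named as the analysis.
- **Sample size**, on the figures: "For a power of 0.80 with an effect size of f" = 0.3. The stated requirement is 79, and 90 is called "being a desirable starting figure".
- **Primary outcome**: "The number of hours worked will be measured at T0 (start), T2 (after 12 weeks) and T3 (after 24 weeks"). The outcome itself is a percentage that sets hours worked at the end of the study against hours worked in the week before T0.
- **Informed consent and randomization**: randomization follows the baseline measurements. On allocation: "Preliminary numbers are assigned to the three groups of equal size in the study".

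The text prints no alpha, no correlation between visits, and no statement of whether f applies to the end value, the change from T0 or a mean over visits.

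**The concern.** The power statement is explicitly about return to work, yet it describes a visit structure that return to work does not have. Hours are not recorded at T1 (6 weeks), so there are three measuring points and not four. One of the three, T0, is taken before allocation, so no treatment difference is expected there. The primary outcome as defined reduces to one value per participant.

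The number of visits and the correlation between them decide how far N can fall below what a single-value comparison needs. If the gain built into 79 is not available for the primary outcome, the trial has less than its stated chance of detecting f = 0.3, and a null result would be read as stronger evidence against that effect than it is.

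**Working it through.** **Inputs.** Power 0.80, f = 0.3, N = 79 and 90, three groups, four measuring points (Sample size); equal allocation (Informed consent and randomization); hours at T0, T2 and T3 (Primary outcome). Assumed: alpha 0.05, F test. The within-person correlation rho is not given, so it is varied. Power comes from the noncentral F distribution with noncentrality λ.

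**1. Reproducing 79.** For a between-group repeated-measures test that averages m equally correlated visits with the full effect at each, λ = N f² m / (1 + (m − 1) rho), df = 2 and N − 3.

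- With m = 4 and rho = 0.6: λ = 79 × 0.09 × 4 / 2.8 = 10.16, power 0.805. N = 78 falls just short of 0.80, so the required N is 79.
- With m = 4, rho = 0.5 gives N = 70 and rho = 0.7 gives N = 87.

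The match is not unique. N = 79 also results from m = 3 with rho about 0.55, from m = 2 with rho about 0.40, and from T3 adjusted for T0 with rho about 0.54.

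**2. Effect of the missing visit alone.** With m = 3 and rho kept at 0.6, λ at N = 79 is 79 × 0.09 × 3 / 2.2 = 9.70, power 0.786. The required N is 82, and power at N = 90 is 0.841. Dropping T1 alone therefore costs little. This formula still credits a full effect at T0.

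**3. One value per participant, no gain.** Take f = 0.3 on the single end-versus-T0 value. Then λ = N f², df = 2 and N − 3.

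| N | λ | Power |
|---|---|---|
| 79 | 79 × 0.09 = 7.11 | 0.644 |
| 90 | 90 × 0.09 = 8.10 | 0.707 |
| 111 | 111 × 0.09 = 9.99 | 0.803 |

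N = 111 (37 per arm) is the smallest N that reaches 0.80. The f detectable with 0.80 power is about 0.36 at N = 79 and 0.33 at N = 90.

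**4. T3 adjusted for T0.** Take f = 0.3 on the T3 scale. Then λ = N f² / (1 − rho²), df = 2 and N − 4.

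| rho | Power at N = 79 | Power at N = 90 | N for 0.80 |
|---|---|---|---|
| 0.3 | 0.69 | 0.75 | 101 |
| 0.4 | 0.73 | 0.79 | 94 |
| 0.45 | 0.75 | 0.81 | – |
| 0.5 | 0.78 | 0.83 | 84 |
| 0.54 | 0.80 | 0.85 | 79 |
| 0.6 | 0.84 | 0.89 | 72 |

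**5. Unadjusted change score, f on the raw scale.** Here λ = N f² / (2(1 − rho)), and the required N is 132 at rho 0.4, 111 at rho 0.5 and 89 at rho 0.6.

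The same printed f, power and contrast thus give required numbers on both sides of 79 and 90, depending on rho and the scale of f.

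**The case against.** The strongest reply is that the article plans a longitudinal multilevel analysis, not a one-way test on a single value. Nothing says that f is on the change scale, and the usual baseline adjustment can deliver the stated power: at rho = 0.6, T3 adjusted for T0 has power 0.84 at N = 79. If the mean of T2 and T3 is analysed with adjustment for T0 and the effect is the same at both visits, power at N = 79 is 0.89 or more for rho from 0.3 to 0.7. A condensed article may also leave alpha and the correlation to the full protocol.

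Much of this stands, and it rules out several stronger readings.

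- A reader might infer that the trial simply needs 111 and that 0.80 is not delivered. The documents do not support that: 111 holds only if no baseline or repeated-measures gain is available.
- A reader might infer that 79 was obtained by counting a visit that does not exist. Four visits with rho 0.6 give 79, but so do three visits, two visits or a baseline-adjusted T3 at other correlations. The missing visit alone moves N only from 79 to 82.
- A reader might average T0, T2 and T3 with no difference at T0, which at rho = 0.6 gives power 0.43 at N = 79 and 0.48 at N = 90. No passage proposes that analysis for the primary outcome.
- That 79 does not divide by three is of no consequence: the starting figure of 90 gives 30 per arm.

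What the reply does not remove is the conflict in print. The article ties a specific N to return to work over four measuring points and elsewhere gives that outcome three. The section describes a T0-versus-T3 comparison and mentions neither a baseline covariate nor a T2/T3 average. Entry also requires at least 50 % absenteeism, which narrows the T0 range, so a T0–T3 correlation near 0.5 needs justification.

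**Conclusion.** The point holds as a conflict between two sections and a power figure that cannot be relied on as printed, not as a proven shortfall. The Sample size section rests on a visit structure that the primary outcome lacks, and its 0.80 requires a gain from a correlation that is not given.

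For the T0-to-T3 three-arm contrast at f = 0.3 and alpha 0.05 (assumed), with f on the analysed value, power at N = 79 is 0.64 without baseline gain, 0.69 at rho 0.3 and 0.80 at rho about 0.54. At N = 90 it is 0.71, 0.75 at rho 0.3, and just over 0.80 at rho 0.45. In the no-gain case the chance of missing f = 0.3 with 90 participants is 1 − 0.71 = 0.29 instead of at most 0.20. With a T0–T3 correlation of about 0.45 or more and baseline adjustment, 90 participants are enough.

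**What to change.** Reconcile the Sample size and Primary outcome sections on the number of measuring points. Keep N = 90 (30 per arm) and rewrite the power paragraph:

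- Name the tested contrast: the three-arm comparison of return to work from T0 to T3, using only visits at which hours are recorded.
- Treat T0 as a covariate and not as an outcome visit.
- State alpha, the scale on which f = 0.3 is defined, and the assumed T0–T3 correlation with its basis.
- Show power over a range. At N = 90, f = 0.3 and alpha 0.05: 0.71 with no baseline gain, 0.75 at rho 0.3, 0.83 at rho 0.5. Add the detectable f of about 0.33 for the no-gain case.

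The cost is one rewritten paragraph and possibly a less favourable stated power. No extra participants or visits are needed.

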#### Ethical considerations

This study has been approved by the Medical Ethics Assessment Committee of the Academic Medical Center (University of Amsterdam). There are no risks associated with participating in the study. The light intensity of 6000 l× is low compared with daylight (0,1 l× – 100 klx) and the spectrum has no Ultra Violet (UV) or Infra-Red (IR) wavelengths. The weak electromagnetic fields are approximately 300 mT. Confidentiality is guaranteed during the course of the study for the participants of all study arms, as no information about the screening or the interventions will be provided to others, such as employers. Furthermore, the study participants of all study arms retain unrestricted access to other care as usual if requested.

## Discussion

This paper describes a protocol for a three-arm RCT consisting of an intervention in which workers with work-related chronic stress are treated with a combination of coaching and light therapy plus.

Pulsed Electromagnetic Field therapy, PEMF. Typically, work-related chronic stress is understood to be a form of emotional exhaustion and fatigue that is not recovered from within 6 months. Both work-related stressors and personal characteristics play a role in the development of work-related chronic stress. There are substantial limitations in professional and/or social functioning. In the Netherlands this disorder accounts for an average of 185 days of absenteeism per person/year and is burdensome and costly for both the employee and the employer.

There are few technical interventions available for work-related chronic stress. One of the few non-technical interventions is the cognitive-behavioural approach, often supplemented with sedatives. Despite the effectiveness of this guidance, it takes a relatively long period of time before workers recover. Shortening the duration of the reintegration time offers advantages for employees, employers and society in general.

The combination of light therapy and pulsed electromagnetic field therapy is unique and combines two promising treatments. The treatment platform used in the study is easy to use, safe and comfortable. There are no known side effects. The method can be applied quickly and has little effect on the daily life of the client. Unlike coaching, the treatment platform can be used anywhere. In addition, it requires no deployment of personnel and it can be used at any time of the day. Most people appreciate lying on the treatment platform. It relaxes them and they experience rest, and no sedatives are needed. Often the participant falls asleep. If proven effective, the treatment can be applied as a new therapeutic tool for people with work-related chronic stress. The platform can be used by coaches, occupational physicians and other health professionals and therapists in daily practice.

Because the participants in this study will be from a heterogeneous sample of workers (recruited through social media, newspapers, general practitioners and occupational health service) in a large region in the Netherlands, the results are thought to be generalizable if the same kinds of treatment centres are available.

### Methodological considerations

A strength of the RCT design is the external validity, which is expected to be high due to the low comorbidity of the participants and uniform situational aspects of the study centre. However, contamination due to communication between participants cannot be ruled out completely as the study is conducted in one centre. An additional strength is the light condition in the CoPL group, which cannot be switched off completely. Only a small dose of non-effective light is used and this cannot be rated as effective or non-effective by the participant. The possibility exists that the combination with light therapy plus pulsed magnetic field therapy without coaching also is effective.

Another strength of the study is the use of hair cortisol analysis. Hair cortisol has the potential to fill the methodological gap of measuring chronic stress and is a unique, non-invasive means of capturing long-term cortisol secretion. Studies have shown that individuals who have elevated cortisol secretion due to stress demonstrate increased hair cortisol [23, 24]. As a biomarker of chronic stress, hair cortisol provides supplementary and objective insights beyond self-reported psychological levels of stress. Hair cortisol analysis can contribute to a more complete understanding of how long-term cortisol secretion mediates stress-related effects on health and well-being.

This study will provide information about the effectiveness of a new combined intervention of coaching with light therapy plus pulsed electromagnetic field therapy and on return to work, fatigue, stress, and quality of life. The results will be available in 2016. The intention is to implement the intervention in occupational care if it is shown to be effective.

